## Abstract

**Background:**

Measurement of muscle mass and function, and thereafter, screening and diagnosis of sarcopenia, is a challenge and a need in hospitalized older adults. However, it is difficult in complex real-world old patients, because usually they are unable to collaborate with clinical, functional, and imaging testing. Ultrasound measurement of *quadriceps rectus femoris* (QRF) provides a non-invasive, real-time assessment of muscle quantity and quality, and is highly acceptable to participants with excellent inter-rater and intra-rater variability. However, normative data, protocol standardization, and association with longitudinal outcomes, needs further research and consensus.

**Methods:**

Prospective exploratory multicenter study in older adults admitted to Acute Geriatric Units (AGUs) for medical reasons. 157 subjects from 7 AGUs of Spain were recruited between May 2019 and January 2022. Muscle ultrasound measurements of the anterior vastus of the QRF were acquired on admission and on discharge, using a previously validated protocol, using a Chieson model ECO2 ultrasound system (Chieson Medical Technologies, Co. Ltd, Wimxu District Wuxi, Jiangsu, China). Measurements included the cross-sectional area, muscle thickness in longitudinal view, intramuscular central tendon thickness, echogenicity, and the presence or absence of edema and fasciculations. Functional, nutritional, and DXA measurements were provided. Clinical follow-up was completed at discharge, and 30 and 90 days after discharge. Variations between hospital admission and discharge ultrasound values, and the relationship with clinical variables, will be analyzed using paired *t*-tests, Wilcoxon tests, or Mc Nemar chi-square tests when necessary. Prevalence of sarcopenia will be calculated, as well as sensitivity and specificity of ultrasound measurements to determine sarcopenia. Kappa analysis will be used to analyze the concordance between measurements, and sensitivity analysis will be conducted for each participating center.

**Discussion:**

The results obtained will be of great interest to the scientific geriatric community to assess the utility and validity of ultrasound measurements for the detection and follow-up of sarcopenia in hospitalized older adults, and its association with adverse outcomes.

**Trial registration:**

NCT05113758. Registration date: November 9^th^ 2021. Retrospectively registered.

## Background

The human aging process involves a decrease in lean mass together with a parallel increase in fat mass [1]. The skeletal muscle system from the third decade of life onwards, undergoes a slow but progressive loss of muscle mass and strength, a circumstance that is accentuated from the age of 65–70 years [2]. From the age of 50, muscle mass decreases by 1–2% annually, and muscle strength by 1.5–3% [3]. In men the process is more progressive, while in women there is an abrupt decrease coinciding with the menopause [3]. This process of loss of muscle mass was defined as sarcopenia [4], and since 2016 it is recognized as an independent condition by an International Classification of Disease, Tenth Revision, Clinical Modification (ICD-10-CM) Code (code M62.84) [5].

Although a consensus global definition of sarcopenia is still evolving [6], the European Working Group on Sarcopenia in Older People (EWGSOP) considers it as a “muscle disease (muscle failure) rooted in adverse muscle changes that accrue across a lifetime. Low muscle strength is the key characteristic of sarcopenia, the detection of low muscle quantity and quality in used to confirm the sarcopenia diagnosis, and poor physical performance is indicative of severe sarcopenia” [7]. This lack of consensus must not hinder the importance of diagnosing and treating sarcopenia in clinical practice [6, 8], because of its demonstrated association with falls and fractures, disability in activities of daily living (ADL), frailty, mobility disorders, cardiac and respiratory diseases, cognitive impairment, institutionalization, quality of life, healthcare costs, and death [7, 9–12].

Several tools are being used for the assessment of muscle mass and quality, including bioelectrical impedance analysis (BIA), magnetic resonance imaging (MRI), computed tomography (CT), dual energy x-ray absorptiometry (DXA), and ultrasound imaging. Recent publications present that ultrasonography may be a valid and reliable imaging method for the assessment of skeletal muscle mass [13–15].

However, the emerging field of ultrasound assessment of muscle mass and quality makes mandatory the need for a standardization of the measurement technique, the identification of the best muscles for determinations, and the cut-off values in different populations, settings, and conditions [16]. Ultrasonography is an easy portable technique, non-invasive, radiation-free, and cost-effective, that not only measures thickness, cross-sectional area and volume, fascicle length, and pennation angle, but also can determine mechanical properties, echogenicity (fat infiltration, fibrosis, myonecrosis), and microcirculation [13]. In older adults, changes in all these parameters can be detected compared to younger adults, mainly in lower limb muscles with antigravitary function, such as the quadriceps femoris and gastrocnemius medialis. Thereafter, these parameters could be theoretically useful for detecting sarcopenia in this population [17].

However, regarding muscle ultrasound measurements in older populations, many questions remain active. The prevalence of sarcopenia ranges from 10 to 40%, with wide ranges due to different measurement methodologies, diagnostic criteria, settings, ethnicity, age, sex, clinical conditions, and selected populations [14, 18]. Reliability and validity values from ultrasound studies have been obtained under strictly controlled conditions, which are likely to decrease in real clinical practice [13, 19], although ultrasound feasibility in acute geriatric settings has been analyzed with promising results [20]. Acknowledging that muscle quality measurements (ability of the tissue to perform its functions including contraction, metabolism, and electrical conduction) seem more important than quantity parameters, functional determinations remain a challenge [21].

Hospitalization for acute illnesses significantly affect the muscle status of critically ill patients [22], and the occurrence of incident sarcopenia in older adults measured with BIA [23], but longitudinal information with ultrasonography in hospitalized older adults is lacking. Finally, imaging diagnostic techniques like DXA, BIA, CT or MRI, may be difficult to acquire in hospitalized older adults, while new assessment protocols using ultrasound imaging have been described in Critical Care Units [24].

Consequently, the aim of the ECOSARC Project is to longitudinally estimate, by means of portable ultrasound under real-life conditions, parameters of muscle quantity and quality (rectus femoris muscle area, thickness and echostructure) in older adults hospitalized in Acute Geriatric Units (AGUs) for medical reasons, the muscle changes between admission and discharge, the prevalence of sarcopenia on admission, the association between muscle parameters with clinical variables and outcomes, and the correlation between ultrasound measurements and other techniques like DXA.

## Methods/design

### Objectives

The main objective of the study is to estimate, by means of portable ultrasound, parameters of muscle quantity and quality of the anterior vastus of the quadriceps rectus femoris (avQRF), including muscle area, thickness, and echostructure, in older adults hospitalized in AGUs for medical reasons.

Secondary objectives are 1) to determine the prevalence of sarcopenia on admission, using the EWGSOP-2 criteria [7], 2) to determine the incidence of sarcopenia on discharge, 3) to assess the evolution of muscle mass of the avQRF between admission and discharge, 4) to evaluate changes in nutritional status, lab results, hand grip strength, gait speed, ADL, frailty, and physical performance from admission to discharge, and at 30 and 90 days for ADL and frailty, and their relationship with ultrasound muscle measurements, and 5) to analyze the relationship between ultrasound muscle measurements and other methods of muscle assessment like DXA or SARC-F. These analyses will help in the validation process of ultrasonography for muscle mass and quality assessment.

### Study design

Prospective exploratory multicenter study in older adults admitted to an AGU.

### Setting

The study was conducted in the Geriatric Departments of 7 hospitals in Spain: Complejo Hospitalario Universitario de Albacete (Albacete), Hospital Universitario de Getafe (Getafe), Hospital Universitario Infanta Sofía (San Sebastián de los Reyes), Hospital Universitario Infanta Leonor (Madrid), Hospital Universitario La Paz (Madrid), Hospital Universitario Puerta de Hierro (Majadahonda), and Hospital Virgen del Valle (Toledo).

### Participants

Patients admitted to an AGU of the 7 participating centers between May 2019 and January 2022, meeting the inclusion criteria: (i) Age ≥ 69 years, (ii) Holden's Functional Ambulation Classification Scale level 1 or higher, and (iii) Informed consent signed by the patient or legal representative.

Exclusion criteria were: (i) Terminal condition or life expectancy of less than 6 months, (ii) impossibility or refusal to undergo muscle ultrasound, (iii) refusal for follow-up, (iv) severe dementia stage, with a Reisberg´s Global Deterioration Scale (GDS) scoring 7, and/or (v) impossibility in the opinion of the investigators to complete the necessary procedures of the study.

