### Independent variables

Demographic, social, and anthropometric data: date of birth, sex, weight, height, body mass index (BMI), ethnicity, lives alone or accompanied, lives at home or in a long-term care. We will use these variables as control ones.Holden Functional Ambulation Classification (FAC) [25] is a functional assessment classification of gait ability, that quantifies the degree of gait dependence from 0 (totally dependent and unable to walk alone) to 5 (totally independent walking). This variable will be used as inclusion criteria.Charlson Comorbidity Index: this is a system for evaluating life expectancy at 10 years, depending on the age of the subject being evaluated and the comorbidities present [26]. It consists of 19 items (apart from age), which if present influence the subject's life expectancy. Initially it was adapted to assess survival at 1 year, but later in its final form it was adapted to assess survival at 10 years [27]. Each item has a given score, and the sum establishes the degree of comorbidity. In general, absence of comorbidity is considered to be 0–1 point, low comorbidity, 2 points, and high comorbidity equal to or greater than 3 points. Survival at 10 years is calculated using calculators [28]. This variable will be used in multivariate analysis as a control one.Clinical data not included in the Charlson index were recorded, including hip prosthesis, spinal estenosis or myelopathy, osteoporosis (or requires medication), vitamin D deficiency (or requires drug or nutritional supplementation), type of dementia if applicable (Alzheimer's disease, vascular or mixed), dyslipidemia (or drug required), insomnia (or requires medication), depressive syndrome (or requires medication), hearing deficit, complete deafness, significant vision loss, blindness, parkinsonism, epilepsy, and other relevant pathologies. This variable will be used in multivariate analysis as a control one.Main clinical diagnosis at the time of hospital admission. This variable will be used in multivariate analysis as a control one.Drugs prescribed up to the time of admission to the hospital. This variable will be used in multivariate analysis as a control one.Barthel Index: the Barthel index assesses basic ADL [29]. It is a hetero-administered questionnaire with 10 Likert-type items. The range of possible index values is between 0 and 100, with 5-point intervals, being the lower the score, the greater the dependence. This variable will be used to evaluate the secondary objective number 4.Reisberg GDS: it is the most widely used instrument to assess cognitive status and detect the presence of dementia of any etiology, although it was initially constructed to assess Alzheimer's disease [30]. It consists of 7 categories ranging from no cognitive impairment (GDS 1) to very severe cognitive impairment (GDS 7), and is evaluated by the physician. This variable will be used as inclusion criteria.FRAIL instrument: it is a simple frailty screening questionnaire developed by the Consensus Conference on Frailty working group and consists of 5 simple questions [31]. The answer can only be yes (scores 1 point) or no (0 points). 0 points indicates no frailty, 1–2 points prefrailty, and 3 or more points identify frailty. This variable will be used to evaluate the secondary objective number 4, and also as a control variable in multivariate analysis.SARC-F instrument: used for sarcopenia screening, understood as low muscle performance in the presence of a loss of muscle mass. It is a simple 5-question instrument, with three possible answers (score 0, 1 or 2 points) [32]. A score of 4 or higher is considered sarcopenia. This variable will be used to evaluate the secondary objective number 5.Short Physical Performance Battery (SPPB): developed by the National Institute on Aging, is an objective assessment tool for evaluating lower extremity physical performance in the older adult [33]. The SPPB consists of three tests: 1) hierarchical balance test, 2) short 4-m walk at usual pace, and 3) rising from a chair five consecutive times. Scores range from 0 (worst performance) to 12 (best performance). Low scores on the SPPB have high predictive value for a wide range of health consequences including disability in ADL, loss of mobility, hospitalization, length of hospitalization, nursing facility admission, and death. This variable will be used to evaluate the secondary objective number 4.Hand grip strength (kg) is an indicator of global strength, nutritional status, and predictor of changes in functionality in older adults. A digital JAMAR dynamometer was used. This assessment is performed seated in a chair, with shoulder and forearm in neutral position and elbow in 90 degrees of flexion. The position of the dynamometer was determined according to the size of the hand, allowing a comfortable and functional grip of the instrument with an adequate closure of the metacarpophalangeal and interphalangeal joints in the first position, favoring the contact between the first phalanx of the index finger and thumb. The participant performed a maximum grip force for 3 s, with 1 min rest between each repetition, making two attempts, where the best of both is the one that was used for the study [34]. This variable will be used to evaluate the secondary objective number 4.Eating Assessment Tool- 10 questionnaire (EAT-10®): this is a verbal, analog, unidimensional, direct-scored self-assessment scale to evaluate specific symptoms of dysphagia [35]. It is a 10-question questionnaire. The patient must respond to each question on a 5-point scale (0–4 points), with 0 indicating no problem and 4 indicating a serious problem. Higher scores indicate greater perception of dysphagia. This variable will be used to evaluate the secondary objective number 4.Mini Nutritional Assessment Tool—Short Form Questionnaire (MNA-SF®): this is a set of questions and measurements that assesses nutritional status in a simple way. It is a validated instrument where the highest score indicates normal nutritional status (12–14 points) and the lowest score indicates malnutrition (0–7 points) [36–38]. This variable will be used to evaluate the secondary objective number 4.A Semi-quantitative intake questionnaire was recorded daily in selected centers. This questionnaire determines daily the percentage of prescribed food that has been eaten in each meal of the day with five categories [all (> 80%), almost all (80–60%), half (60–40%), almost nothing (40–20%) or nothing (< 20%)]. It has to be performed by a dietitian, and calculates the mean of the complete hospital stay intake, to yield a final percentage of this intake [39]. This variable will be used to evaluate the secondary objective number 4.Lab tests data (in each center, usual admission lab parameters were used): hemoglobin, platelets, leukocytes, neutrophils, lymphocytes, albumin, total protein, total cholesterol (LDL and HDL if available), transferrin, ferritin, erythrocyte sedimentation rate (ESR), C-reactive protein (CRP), glycemia, creatinine, urea, thyroid hormones, creatin-phosphokinase, folic acid, and vitamin B12. These variables will be used to evaluate the secondary objective number 4.DXA was realized in selected centers (Horizon® DXA system, Hologic Inc., U.S.): variables included in the analysis were total muscle mass, appendicular lean mass (aLM), aLM/Body Mass Inex (BMI), aLM/height^2^, total fat mass, percentage of fat mass (%), start date, end date. These variables will be used to evaluate the secondary objective number 5.Patient conditions during hospital admission: number of days of bed rest, bed-chair, and with mobilization; number of days of rehabilitation, occupational therapy, and physical exercise; number of days fasting, liquid diet and basal diet. These variables will be used as possible explicative control variables for muscle changes during hospitalization.

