### Statistical methods

No value imputation system was established, so the final sample size was the number of patients with values at admission and discharge for the different parameters measured. We will determine the normal distribution goodness-of-fit of the continuous variables using the Kolmogorov–Smirnov and Shapiro–Wilk tests as needed. We will calculate the mean and standard deviations in the case of normally distributed variables and the median and the interquartile range in skewed variables. 95% confidence intervals will be calculated when necessary.

Variations between hospital admission and discharge ultrasound values, DXA and anthropometric parameters, functional scales, nutritional status, cognitive status, and in general any other quantitative variable, will be calculated using paired *t*-tests, Wilcoxon tests, or Mc Nemar chi-square tests when necessary.

The prevalence of sarcopenia will be calculated as percentages. Sensitivity and specificity of ultrasound measurements to determine sarcopenia will be calculated. Kappa analysis will be used to analyze the concordance between measurements. The coefficient of variation of the ultrasound device will be calculated. Sensitivity analysis will be conducted for each participating center. All analyses will be performed with SPSS (Statistical Package for Social Sciences) statistical software, version 24.0 or later (IBM Corp. Released 2016. IBM SPSS Statistics for Windows, Version 24.0. Armonk, NY: IBM Corp).

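### Change in gait speed is analysed only in patients with a walk time at both visits, so those who lose or regain walking leave that component of objective 4

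*Protocol article*

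**What the plan says.** All references are to the Protocol article.

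- **Objectives.** Secondary objective 4 is "to evaluate changes in nutritional status, lab results, hand grip strength, gait speed, ADL, frailty, and physical performance from admission to discharge", together with the relation of these changes to the ultrasound measurements. Gait speed is listed separately from physical performance.
- **Independent variables and Table 1.** Gait speed has no entry of its own in either place. The only walk described is the second SPPB test, "2) short 4-m walk at usual pace". The SPPB is scheduled at baseline and discharge and its total runs from 0 to 12.
- **Participants.** Entry requires "Functional Ambulation Classification Scale level 1 or higher". The scale is described as running "from 0 (totally dependent and unable to walk alone) to 5 (totally independent walking"; the levels in between are not defined. Table 1 schedules it at baseline only.
- **Statistical methods.** No imputation is set up, and "the final sample size was the number of patients with values at admission and discharge for the different parameters measured". Changes are tested with paired t-tests, "Wilcoxon tests, or Mc Nemar chi-square tests when necessary".
- **Discussion.** The authors expect that grip strength and function tests, gait speed among them, will be hard to complete for many inpatients.

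**The concern.** Gait speed is undefined for a patient who cannot walk the 4 m. Under a rule that needs a value at both visits and imputes nothing, such a patient has no change score. Whether a patient is in the analysis therefore depends on the outcome itself: those who walk at admission but not at discharge, or the reverse, are removed, and they have the largest changes in mobility. In a study of muscle and function during acute admission, inability to walk is an observed poor result and not an absent one.

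At stake is what the gait-speed result means. It would describe patients who walk at both visits, without saying so. Its relation to ultrasound change would be estimated after removing the patients at both extremes of functional change. Gait speed and the SPPB total could also be reported on different patients in the same table.

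**Working it through.** **1. The plan's own figure.** The article gives no sample size for gait speed. The only one is for cross-sectional area (Sample size calculation): difference 0.2 cm², SD 0.8, two-sided alpha 0.05, power 0.80, drop-out 20%.

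n = (SD × (1.960 + 0.842) / difference)² = (0.8 × 2.8016 / 0.2)² = 125.6, and 125.6 / 0.80 = 156.98, that is 157.

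The stated 157 reproduces as a paired comparison with drop-out already included. It leaves about 126 patients with both visits, which is used below as a convenient base. It neither supports nor refutes the point about gait speed.

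**2. Following the rule as written.**

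| Walk at admission | Walk at discharge | Pair of speeds? | In gait-speed change? |
|---|---|---|---|
| able | able | yes | yes |
| able | unable | no | no |
| unable | able | no | no |
| unable | unable | no | no |

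Only the first row remains. The second and third rows hold the patients whose walking status changed.

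**3. Illustration of size.** The documents give no gait speeds and no share of patients unable to walk, so every input here is an assumption: patients walking at both visits change by +0.05 m/s; a patient who loses or regains walking moves between 0.40 and 0 m/s; nobody is unable at both visits. With a the share losing and b the share regaining walking:

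change with inability counted as 0 m/s = (1 - a - b) × 0.05 - a × 0.40 + b × 0.40

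| Lose (a) | Regain (b) | Pairs of 126 | Complete-pair change | Inability as 0 m/s |
|---|---|---|---|---|
| 10% | 0% | 113 | +0.050 | 0.045 - 0.040 = +0.005 |
| 20% | 0% | 101 | +0.050 | 0.040 - 0.080 = -0.040 |
| 0% | 10% | 113 | +0.050 | 0.045 + 0.040 = +0.085 |
| 0% | 20% | 101 | +0.050 | 0.040 + 0.080 = +0.120 |
| 10% | 10% | 101 | +0.050 | 0.040 - 0.040 + 0.040 = +0.040 |

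The complete-pair figure is the same in every row: it cannot respond to lost or regained walking. With no regain, the sign changes once 0.05 × (1 - a) = 0.40 × a, that is a = 0.05 / 0.45 = 11%. With equal losses and gains the gap is small.

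**4. Loss of pairs.** This is a lesser matter. For a standardised change of 0.25 (0.2 / 0.8, borrowed from the area calculation), power falls from 80% with 126 pairs to 76% with 113 and 71% with 101.

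**The case against.** **Coding of inability is detail for the case report form or the analysis plan.** A condensed article need not state it, and recording an observed inability is not imputation, so the no-imputation rule does not forbid it. This stands in part. If inability was already coded as a value, the concern is met and needs only a sentence. But the article does state the analysis set, names gait speed as a separate target and expects tests of this kind often not to be completed. Followed as written, the stated rule drops these patients.

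**Investigators may exclude patients at entry for "impossibility in the opinion of the investigators to complete the necessary procedures of the study".** That may remove some non-walkers at admission. It is not tied to walking, and as an entry criterion it cannot deal with walking lost by discharge.

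**Zero is only one convention.** True. A walkers-only change is also a legitimate description, provided it is labelled as such.

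A reader might infer more than the documents support:

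- *These patients drop out of objective 4.* They do not. The rule works parameter by parameter, and the Barthel index, FRAIL, grip strength, nutrition and laboratory values need no walk time. The SPPB total has a floor of 0, although the article does not say how an unattempted walk is scored.
- *The entry threshold is the error, because level 1 patients cannot do a timed walk.* The intermediate levels are undefined and the article does not say whether aids or help are allowed. A patient entering at level 5 who loses walking is dropped in the same way.
- *The reported change will have the wrong sign.* That occurs only under some of the assumed mixes above.

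**Conclusion.** The point holds for one component of one secondary objective in an exploratory study. As written, the rule selects patients on the outcome: the gait-speed change, and its relation to ultrasound, would describe only those who walk at both visits. Entry from level 1 of the ambulation scale makes exclusions more likely but does not cause the problem. The bias can run in either direction and its size cannot be derived from the documents. The range from -0.040 to +0.120 m/s against a fixed +0.050 rests wholly on the assumed speeds and shares. The conclusion also assumes that an inability to walk is left without a speed in the data. It is worth correcting because the remedy is cheap and the analyses are still described as to be done.

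**What to change.** Add to Statistical methods:

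1. For patients alive and assessed at a visit, inability to do the 4-m walk counts as an observed worst result, for example 0 m/s. A walk not attempted for other reasons, and a visit not made, stay missing.
2. Change in gait speed is analysed on all such patients with the Wilcoxon signed-rank test already planned.
3. Able/unable status at admission and discharge is shown in a two-by-two table with the McNemar test already planned, with the number unable at each visit. Patients unable at both visits have zero change and add little to the signed-rank test, so this table is where they are seen.
4. The mean change in patients walking at both visits is kept as a secondary result, labelled as conditional on walking.

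The cost is one coding rule and one extra table. The drawback is a variable with many values at zero, for which a rank test is better suited than a paired t-test. The fix depends on inability having been recorded with the SPPB data. If it was not, the article should say so and present the gait-speed change only as conditional on walking at both visits.
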